### Safety evaluation

2.6

Safety evaluation was performed by observing adverse events (detailed records at any moment), in addition to evaluating symptoms, abnormal laboratory findings or other examinations (physical and laboratory examinations including blood routine, liver and kidney function, and biochemical examination). Adverse events will be identified by comparison, and causal analysis of adverse events will be performed according to “positively relevant,” “very likely relevant,” “probably relevant,” “probably irrelevant,” and “positively irrelevant.”

### Sample size calculation

2.7

The sample size of this study was calculated based on the recurrence rates which is the primary outcome. According to the previous study, taking methotrexate as an example, the recurrence rate of conventional therapies is 73.7%,^[5]^ The recurrence rate of integrated Chinese Medicine is 28.6%,^[20]^ We suppose the recurrence rate of TCM group was 20%. Using non-equality test design by the PASS software, we set the α=0.05 and the power 1-β=0.8, the ratio of cases among each group is 1:1:1, the number of cases calculated is 390 in each group. We suppose a 30% of lost in the follow-up Of the study, the ultimately needed cases in each group is 507.

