## Introduction

1

Psoriasis is a common chronic, recurrent, immune-mediated dermatological disease. Environmental and genetic factors and their interactions are thought to contribute to the disease. Typical clinical manifestations are scaly erythema or plaques. They may be localized or present throughout the body. The disease is difficult to treat and often has lifetime risks. It affects about 3% of the worlds’ population, with a higher prevalence in Europe and the United States compared to China (0.123-0.47%). However, the incidence rates have been increasing over the years.^[1]^ Patients with psoriasis are usually accompanied with cardiovascular diseases, diabetes, metabolic syndromes, mental diseases and enteritis.^[2–4]^ It seriously affects the physical and mental health of patients and is a burden on medical resources. The 1-year recurrence rate of psoriasis is as high as 73.7%,^[5]^ and is a key concern for patients with psoriasis. High-risk factors for recurrence include tobacco use, alcohol, dampness, upper respiratory tract infections, certain medications, mental stress, being overweight and increased body fat ratios.

Conventional therapy that is used to treat psoriasis patients includes retinoic acid, phototherapy, immunosuppressive agents and targeted biological agents. However, these first-line therapies are expensive and have several adverse side effects.^[6,7]^ Previous studies have demonstrated that cyclosporin A, calcipotriol and methotrexate could moderately prolong psoriasis recurrence through sequential therapy, topical drug therapy, 308 excimer laser and biological agents .^[8]^ The majority of conventional therapies include a dosage reduction scheme, lifestyle changes and health education to delay recurrence. These include relaxation, behavioral changes, balanced diets, fish oils, and foods rich in n-3 fatty acid supplements, in addition to smoking and drinking cessation and the use of topical emollients.^[9–11]^ However, these measures do not prevent relapse. There is a critical need to find alternative therapies to prevent the recurrence of psoriasis. Latin American Clinical Practice Guidelines on the systemic treatment of psoriasis offers an updated therapeutic information and a reference for therapeutic decisions, with the main goal of improving patient care, controlling symptoms, and improving patients’ quality of life. However, it does not provide guidelines on how to prevent recurrence.^[12]^

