#### Main outcomes

2.5.1

Recurrence rate in 6 months. Definition of recurrence: Patients have got relief psoriasis area and disease severity index score (PASI75), while the total PASI score increased to 50% of the original PASI.^[19]^

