#### General principles

2.10.1

SAS 9.2 software will be used for statistical analyses. Qualitative indicators will be described using frequency tables, percentages or composition ratios and quantitative indicators will be described using mean, standard deviation, median, lower quartile (P25), upper quartile (P75), minimum value (min), and maximum value (max). The hypothesis test will be a 2-sided test and will include test statistics and their corresponding *P*-values. *P* <.05 will be considered statistically significant.

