Based on an intelligent and information-based data collection and data management platform, this study observed and followed-up on thousands of patients within a short period. Data will be analyzed after centralized integration to compare conventional therapy with that of the combination of Chinese and Western medicine treatment. Patients will be evaluated based on recurrence rate 6 months after PASI75, onset time, maintenance time, the incidence of new rashes during treatment and follow-up, World Health Organization Quality of Life Instruments/BSA/VAS scores and treatment costs. The long-term efficacy of TCM in treating psoriasis vulgaris through intelligent and information-based data collection and management will then be established and evaluated. It determined the advantages of TCM and provided real-world evidence for the long-term efficacy of TCM for the treatment of psoriasis. In addition, the platform could evaluate the mode and cost-effectiveness of psoriasis vulgaris treatment in the real world. Improvement of skin lesions, patient quality of life, recurrence rates of skin lesions and the state of anxiety and depression will also be able to be evaluated in the future. Long-term follow-ups of patients during remission and recurrence will provide clues to inducing factors and effective interventions for patient treatment. Using the multicenter registration platform to collect large amounts of standardized data within a short period will help mine and analyze long-term efficacy data of TCM for the treatment of psoriasis from the perspective of recurrence.

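### The 390 per group gives 80% power for integrated versus TCM only if every counted patient reaches PASI75; the calculation makes no allowance for non-response

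*Protocol article*

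**What the plan says.** All references are to the protocol article.

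- **Sample size calculation (2.7).** The planning recurrence rates are 73.7% for conventional therapy, 28.6% for integrated therapy and a supposed 20% for TCM. The error rates are given as "we set the α=0.05 and the power 1-β=0.8", and the result is that "the ratio of cases among each group is 1:1:1, the number of cases calculated is 390 in each group". A 30% loss to follow-up then raises this to 507 per group, 1521 in total. No other allowance is made.
- **Main outcomes (2.5.1).** The primary outcome is the 6-month recurrence rate, and recurrence is defined as "Patients have got relief psoriasis area and disease severity index score (PASI75), while the total PASI score increased to 50% of the original PASI".
- **Discussion (3).** The start of the window is made explicit: "Patients will be evaluated based on recurrence rate 6 months after PASI75".
- **Eligibility criteria (2.3.1).** PASI75 is not an entry condition. Time to reach it is a secondary outcome (2.5.2), so it is something that happens, or does not happen, after enrolment.
- **Introduction (1).** The same 73.7%, with the same reference as in 2.7, has a time horizon: "The 1-year recurrence rate of psoriasis is as high as 73.7" per cent.

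**The concern.** The sample size section counts enrolled patients less those lost to follow-up. The outcome can be observed only in the subset who first reach PASI75. The number informing the primary comparison is therefore the number enrolled, times the proportion followed, times the proportion reaching PASI75. The last factor is missing.

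Two things are at stake. First, a non-significant integrated-versus-TCM result could be read as similarity shown by an 80%-powered study when the real power was much lower. Second, a comparison among responders conditions on a result of treatment. If the cohorts differ in how many or which patients respond, the recurrence rates compare differently selected groups. The propensity-score matching in 2.10.5 adjusts for covariates and does not by itself remove selection that arises after treatment starts.

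**Working it through.** **Inputs from the article.** Rates of 73.7%, 28.6% and 20%; α = 0.05; power 0.80; 390 and 507 per group; 30% loss (all from 2.7). Two-sided testing: "The hypothesis test will be a 2-sided test" (2.10.1). **Input not in the article.** The PASI75 rate r, taken here over an assumed range and set equal in all cohorts.

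**1. Reproduce 390.** The pooled two-proportion z-test without continuity correction gives

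n = [1.960·√(2p̄(1−p̄)) + 0.842·√(p₁(1−p₁) + p₂(1−p₂))]² / (p₁−p₂)²

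For 0.286 versus 0.20, p̄ = 0.243. The two square roots are 0.6065 and 0.6035, and the difference is 0.086. This gives n = 389.2, rounded up to **390** (power 80.1%), an exact match.

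The other contrasts do not give 390: 73.7% versus 28.6% needs 19 per group, and 73.7% versus 20% needs 13. The sample size therefore rests on integrated versus TCM.

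**2. The follow-up allowance.** 390 × 1.3 = 507, but 507 × 0.7 = 354.9, about 355. Offsetting a 30% loss would take 390/0.7 = 558. Using

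power = Φ{[|p₁−p₂|·√m − 1.960·√(2p̄(1−p̄))] / √(p₁(1−p₁) + p₂(1−p₂))}

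with m = 355 gives **76.3%**, before any non-response.

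**3. Add PASI75 non-response (28.6% versus 20%).** The left-hand pair isolates non-response by keeping 390 before applying r. The right-hand pair is the plan as it stands, 507 × 0.7 × r.

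| Assumed r | 390·r | Power | 355·r | Power |
|---|---|---|---|---|
| 100% | 390 | 80% | 355 | 76% |
| 80% | 312 | 71% | 284 | 67% |
| 60% | 234 | 58% | 213 | 54% |
| 40% | 156 | 42% | 142 | 39% |

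With no loss at all, 390/507 = 77% of each cohort would have to reach PASI75 to leave 390.

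**4. Contrasts with conventional therapy.** As a check on the horizon, assume a constant hazard. Then 73.7% at 1 year becomes 1 − √(1 − 0.737) = 48.7% at 6 months. The required numbers rise from 19 to 91 per group (versus 28.6%) and from 13 to 42 (versus 20%). With 355 per group, power is at least 99.9% for both. At r = 40% (142 per group), it is 94% and 99.9%.

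**The case against.** **The documents give no PASI75 rate, so the loss cannot be sized.** True, and only a range can be shown. The direction does not depend on it: under the plan's own 30% loss, no PASI75 rate gives 80% for integrated versus TCM.

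**Part of the shortfall is not non-response.** Also true. The drop from 80% to 76% comes from multiplying by 1.3, and the left-hand columns of the table separate the two effects.

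**The 28.6% and 20% may be rates among all treated patients.** The article gives no denominator for either. If they were such rates and the outcome were counted that way, 390 treated patients would match them. That would count a patient who never responds as free of recurrence, which does not fit a definition that begins with PASI75. The follow-up arithmetic would still leave 76%. If instead the rates apply to responders and non-responders stay in the denominator as not recurrent, 355 per group gives 57%, 42% and 26% at response rates of 70%, 50% and 30%.

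**Stronger readings that the article does not support.**

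- A reader might infer that the 1-year 73.7% costs the study its power. It does not: that rate does not enter the 390, and both conventional contrasts stay at 94% or above over the range shown, even with 48.7%.
- A reader might infer that the whole study is underpowered. The shortfall concerns integrated versus TCM only. The Discussion's emphasis on conventional versus combined treatment points to a contrast with ample power.
- A reader might convert 28.6% and 20% to 6-month rates as well, to 15.5% and 10.6%, which would give 54% power with 390 per group. This requires both to be 1-year rates, and the article states no horizon for either.
- A reader might conclude that responder selection favours one particular cohort. The direction cannot be known from the article.

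**Conclusion.** The point holds for integrated versus TCM, the contrast that produces the 390. The calculation does not fit the primary outcome as defined, and the stated 80% power is not delivered. As planned, it is 76% if every patient reaches PASI75, and about 67%, 54% and 39% at 80%, 60% and 40%. These figures assume that 28.6% and 20% are rates among responders, that response is equal in the cohorts and that loss is 30%.

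The time horizon is a separate and smaller inconsistency. The Introduction calls 73.7% a 1-year rate, while 2.7 uses it ("the recurrence rate of conventional therapies is 73.7" per cent) for a 6-month outcome. It needs correcting as a statement of the planning basis, with little effect on power.

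**What to change.** In section 2.7:

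- State that 390 means PASI75 responders with 6-month follow-up, and that it refers to integrated versus TCM.
- Restate the expected evaluable number and the power for 507 enrolled over a stated range of PASI75 rates, with the 30% loss applied as a division by 0.7 or its consequence (355 remaining) acknowledged.
- Give the time horizon of each planning rate and align it with 6 months.

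In the outcome and analysis sections:

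- Report PASI75 attainment for each cohort beside its recurrence rate.
- Add a supportive analysis in all enrolled patients, with success defined as PASI75 reached and no recurrence in the following 6 months, so that the conclusion does not rest on responders alone.

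The cost is rewording, one extra analysis from data already collected, and a less favourable stated power for integrated versus TCM. Enrolment and patient management need not change.

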### Study design

2.1

This is a prospective, multicenter cohort study. The study was initiated in July 2019 and will end in December 2021. We plan to recruit 1521 psoriasis vulgaris patients from 14 hospitals in Beijing, Tianjin and Hebei province. All patients will be given therapies based on TCM and Conventional therapy guidelines and then followed-up for 1 year. Prior to recruitment, each participating hospital should be required to obtain ethics approval. Each participating hospital will follow a standard set of procedures. The flow chart of the study is depicted in Figure 1.

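### The 30% loss allowance multiplies 390 by 1.3 instead of dividing by 0.7, so 507 per group does not keep the 390 needed for 80% power

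*Protocol article*

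**What the plan says.** Section 2.7 (Sample size calculation) bases the size on recurrence, the primary outcome. It takes rates of 73.7% for conventional therapy, 28.6% for integrated therapy and a supposed 20% for TCM. On the error rates it says "we set the α=0.05 and the power 1-β=0.8", and on allocation "the ratio of cases among each group is 1:1:1". The result is 390 per group. The allowance for attrition follows: "We suppose a 30% of lost in the follow-up Of the study, the ultimately needed cases in each group is 507".

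Section 2.1 (Study design) carries the result forward: "We plan to recruit 1521 psoriasis vulgaris patients from 14 hospitals in Beijing, Tianjin and Hebei province". The abstract gives the same total, which is 3 × 507. Section 2.10.1 (General principles) settles the sidedness: "The hypothesis test will be a 2-sided test".

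**The concern.** The allowance adds 30% of the required number to the required number. Loss to follow-up works the other way: it removes a fraction of those enrolled. To finish with n patients after losing a fraction d, one must enrol n / (1 − d), not n × (1 + d). The gap between the two grows with d and is material at 30%.

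Section 2.7 tells the reader that the study keeps its planned power after the loss it expects, and by its own numbers it does not. The headline enrolment of 1521 comes from this step. If the contrast that sets the size came out non-significant, the result would be read against a power claim that the design does not meet.

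**Working it through.** **Inputs.** Rates of 20%, 28.6% and 73.7%, α = 0.05, power 0.80, equal groups, 390 before loss, 30% loss and 507 after loss, all from section 2.7. Two-sided testing from section 2.10.1. Total 1521 from section 2.1.

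**Step 1: reproduce 390.** Pooled two-proportion formula, no continuity correction:

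n = [z(0.975) √(2p̄(1 − p̄)) + z(0.80) √(p₁(1 − p₁) + p₂(1 − p₂))]² / (p₁ − p₂)²

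For TCM versus integrated therapy, p₁ = 0.20, p₂ = 0.286 and p̄ = 0.243:

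- √(2 × 0.243 × 0.757) = 0.6065
- √(0.160 + 0.2042) = 0.6035
- n = (1.960 × 0.6065 + 0.8416 × 0.6035)² / 0.086² = 389.2, rounded up to **390**, which matches the article.

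The same formula gives 19 per group for integrated versus conventional therapy and 13 for TCM versus conventional therapy. A three-group chi-square test needs about 14 per group. Close variants for TCM versus integrated give 387 (unpooled), 388 (arcsine) and 413 (continuity-corrected). TCM versus integrated is therefore the contrast behind 390, although the article does not say so.

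**Step 2: reproduce 507.** 390 × 1.30 = **507** exactly, and 3 × 507 = **1521**.

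**Step 3: apply the stated loss.** 507 × 0.70 = 354.9, about **355** per group, which is 35 below 390.

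**Step 4: enrolment that would keep 390.** 390 / 0.70 = 557.1, rounded up to **558** per group. As a check, 558 × 0.70 = 390.6. The total is 3 × 558 = **1674**, which is 51 more per group and 153 more overall than planned.

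**Step 5: loss that 507 can absorb.** 1 − 390/507 = **23.1%**.

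**Step 6: power at the stated loss.**

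Power = Φ{[|p₁ − p₂| √n − z(0.975) √(2p̄(1 − p̄))] / √(p₁(1 − p₁) + p₂(1 − p₂))}

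For n = 355: (0.086 × 18.841 − 1.960 × 0.6065) / 0.6035 = 0.715, and Φ(0.715) = 0.763.

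| Contrast | 390 per group | 355 per group |
|---|---|---|
| TCM vs integrated (20% vs 28.6%) | 80.1% | 76.3% |
| Integrated vs conventional (28.6% vs 73.7%) | >99.9% | >99.9% |
| TCM vs conventional (20% vs 73.7%) | >99.9% | >99.9% |

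Exact enumeration of the uncorrected chi-square test agrees for the first row: 80.2% at 390 and 76.4% at 355. With a continuity correction, power at 355 is 73.5%.

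**The case against.** The arithmetic is not in dispute. The 30% could be read as a mark-up on the calculated number, but the sentence speaks of patients lost during follow-up, so that reading is weak. No other section supplies a reserve. The serious objections concern scope and weight.

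- **Scope.** The article does not name the contrast behind 390, and power against conventional therapy is untouched. This stands as a limit on the power statement: the 76% belongs to TCM versus integrated therapy only and rests on an inference, though a strong one. The error in the allowance does not depend on it.
- **Size relative to other uncertainty.** The 20% rate for TCM is only supposed. At a full 390 per group, a true rate of 21% would give 69% power and 19% would give 88%. One percentage point in that guess matters more than the 4 points lost here. That is true, but uncertainty in an assumption does not excuse an arithmetic error made with that assumption fixed.
- **Idealised group sizes.** Cohorts are formed by treatment received (section 2.3.2), recurrence presupposes a PASI75 response (section 2.5.1), and propensity score matching is planned (section 2.10.5). The numbers analysed may differ from 355 for all these reasons. This also stands: 355 checks the stated calculation and does not forecast the analysis sets.
- **Weight.** A correction that changes no enrolment may look minor. However, the sentence is part of the justification of the sample size on the primary outcome, and it is wrong as written.

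**Conclusion.** The concern holds. The loss allowance in section 2.7 is miscalculated: 507 per group keeps 390 only if loss is at most 23.1%, and at the stated 30% it keeps about 355. The shortfall in enrolment is 51 per group, or 153 overall.

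The effect on power is modest and confined to one contrast. For TCM versus integrated therapy, power is about 76% instead of 80%, so the type II error rises from about 20% to about 24%. This figure assumes the article's own rates of 20% and 28.6%, equal groups, a two-sided 5% test without multiplicity adjustment, and that this contrast produced 390.

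**What to change.** Keep 1521 and correct the last sentence of section 2.7, naming the contrast. The wording that keeps the 30% assumption is preferable:

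*With 507 patients enrolled per group and 30% lost to follow-up, about 355 per group remain evaluable, giving about 76% power for TCM versus integrated therapy (20% versus 28.6%, two-sided α = 0.05).*

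An alternative that is equally true arithmetically:

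*Enrolling 507 per group allows for up to 23% loss while keeping 390 per group and 80% power for TCM versus integrated therapy.*

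The alternative replaces the stated 30% with a figure worked back from 507, so the sponsor should use it only if it can support a loss of 23% or less.

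The cost is one sentence. No more patients are needed and nothing changes in conduct or analysis, which suits a study that section 2.1 says began in July 2019. The stated power, or the stated tolerance for loss, becomes somewhat less favourable.

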### Data collection

2.8

We will use the “yiluyun clinical research information management system” as the data management platform. This database is designed by Beijing Institute of TCM, which data will be collected from PC, pad and phone. The hierarchy of users access can be ranked as entry clerk, supervisors and auditors.

The entered data can be returned for modification after submission, but the modification traces need to be kept. According to the Standard operating procedure for data entry, in the process of data entry, the person in charge of data entry shall guide in time and track the work progress and quality of data entry personnel. Once the data is submitted, the editing authority of this page will be cancelled.

### Data validation

2.9

After data export, SAS9.4 software will be used to check the validation, which mainly refers to the following contents: conformation to the inclusion and exclusion criteria, existing of extreme values or logic errors for the measurement values of each visit, concomitant medication, and the occurrence of adverse events during the study.

### Statistical analyses

2.10

#### General principles

2.10.1

SAS 9.2 software will be used for statistical analyses. Qualitative indicators will be described using frequency tables, percentages or composition ratios and quantitative indicators will be described using mean, standard deviation, median, lower quartile (P25), upper quartile (P75), minimum value (min), and maximum value (max). The hypothesis test will be a 2-sided test and will include test statistics and their corresponding *P*-values. *P* <.05 will be considered statistically significant.

#### Non regulatory analysis

2.10.2

For the comparative analysis of 2 groups, qualitative data will be analyzed using the chi-square test, Fisher exact probability, Wilcoxon rank-sum test and CMH chi-square test. Quantitative data in line with normal distribution will be analyzed using *t*-test (homogeneity test of variance between groups, test level at 0.05, and Satterthwaite method will be used for correction when the variance is uneven). Wilcoxon rank-sum test and Wilcoxon signed-rank sum test will be used when the data is abnormally distributed.

The survival analysis will be used to compare statistical significance between the groups (for the appearance of new skin lesions). In addition, the Cox regression model will be used to adjust the impact of baseline PASI values, course of the disease, and body mass index.

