#### Efficacy analysis (Adjustment analysis)

2.10.5

Efficacy analysis indicators will include changes in the main efficacy indicators from the initial visit (baseline) to each follow-up period.

Logistic regression analysis will be used to study the relationship between continuous dependent variables and independent variables. Influencing factors will be analyzed to determine which independent variable influences the probability of dependent variable occurrence. The decision analysis method will be used to estimate the probability of each category of the dependent variable (in the presence of a combination of various independent variables), to predict the outcome. The mixed effect of multiple covariates on treatment outcome will be adjusted using the propensity score matching method. First, we will determine if the distribution of patients with similar tendentiousness score is balanced among the groups. The distribution of patients will then be adjusted according to the tendentiousness score to calculate the effect estimation value. Stratified analysis will be conducted based on patients’ PASI score which will be divided into 4 groups based on the 4 levels of PASI score (less than 10,10–20,20–30 and more than 30).

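### Choosing the t-test by a variance pre-test at 0.05 misses the nominal 5% slightly when cohort sizes and variances both differ (minor)

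*Protocol article*

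**What the plan says.** Section 2.10.2 (Non regulatory analysis) covers unadjusted comparisons of two groups. It opens the rule with "Quantitative data in line with normal distribution will be analyzed using" the t-test, and adds in brackets: "homogeneity test of variance between groups, test level at 0.05, and Satterthwaite method will be used for correction when the variance is uneven". The article does not name the pooled t-test, but a correction applied only after a significant variance test implies the pooled form otherwise. Non-normal data go to Wilcoxon tests.

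Section 2.10.1 sets the standard the tests must meet: "The hypothesis test will be a 2-sided test and will include test statistics", with significance declared below 0.05.

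Three other places bear on group size:
- Section 2.7 plans equal cohorts: "the ratio of cases among each group is 1:1:1, the number of cases calculated is 390 in each group", raised to 507 for losses.
- Sections 2.3.1 and 2.3.2 enrol patients consecutively and assign them to cohorts by the treatment they received. No cohort quota is described.
- Section 2.10.5 (Adjustment analysis) adds a stratified analysis by PASI score, "which will be divided into 4 groups based on the 4 levels of PASI score". It does not say that t-tests are run within those strata.

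**The concern.** The pooled t-test estimates one common variance. If the groups differ in size and in variance, its standard error is wrong. It is too small when the smaller group is the more variable, and too large when the smaller group is the less variable. The variance test is meant to catch this, but at level 0.05 it often misses modest differences, and the wrong standard error is then used. The reported P-value follows neither the pooled nor the Satterthwaite test, but a data-dependent mixture of the two.

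At stake is the error rate of the unadjusted comparisons of those secondary quantitative outcomes that are judged normal. The article does not say which outcomes those will be.

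**Working it through.** **Inputs from the article.** Two-sided testing at 0.05 (2.10.1); variance test at 0.05 followed by Satterthwaite if significant (2.10.2); 1:1:1 with 390, then 507, per cohort (2.7).

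**Inputs assumed.** SD ratios and unequal group sizes, because the article gives neither. The variance test is taken as the folded F-test, because the article does not name one. Data are normal with equal means. Throughout, the SD ratio r is the smaller group's SD divided by the larger group's.

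**Step 1: the plan's own figure.** The article states no error rate for the t-test rule. Its one computed figure, the sample size, reproduces with "we set the α=0.05 and the power 1-β=0.8" and rates of 28.6% and 20% (mean 0.243, difference 0.086):

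n = [1.960·√(2·0.243·0.757) + 0.842·√(0.286·0.714 + 0.20·0.80)]² / 0.086² = (1.189 + 0.508)² / 0.007396 ≈ 389.3, so 390.

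Then 390 × 1.3 = 507 and 3 × 507 = 1521. This confirms that equal cohorts and a two-sided 0.05 level are what the design assumes.

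**Step 2: why equal sizes are safe.** With n per group and variances r² and 1, the true variance of the mean difference is (r² + 1)/n. The pooled formula estimates [(r² + 1)/2]·(2/n), which is the same.

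**Step 3: why unequal sizes with unequal variances are not.** Take 100 vs 600 and r = 1.1.
- True variance: 1.21/100 + 1/600 = 0.01377.
- Pooled estimate: [(99·1.21 + 599·1)/698]·(1/100 + 1/600) = 1.0298·0.011667 = 0.01201.
- Ratio of standard errors: √(0.01377/0.01201) ≈ 1.070.
- Effective critical value: 1.960/1.070 ≈ 1.83, so the pooled test alone has a two-sided error of about 6.7%.

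In simulation the variance test rejects in only about 26% of such samples, so the pooled test is still used in about 74%.

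**Step 4: the two-stage rule by simulation.** At least 200,000 replicates were run per cell, so the simulation error is about 0.05 points. Entries are type I error in % at nominal 5%.

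| Sizes | r = 0.8 | r = 0.9 | r = 1.0 | r = 1.1 | r = 1.2 | r = 1.3 | r = 1.5 |
|---|---|---|---|---|---|---|---|
| 390 / 390 | 5.0 | – | 5.0 | 5.0 | 5.0 | 5.1 | 5.0 |
| 507 / 507 | 5.0 | – | 5.0 | 5.0 | 4.9 | 5.0 | 5.1 |
| 300 / 600 | – | 4.8 | 5.0 | 5.2 | 5.0 | 5.0 | 5.0 |
| 200 / 580 | 5.0 | – | 5.0 | 5.5 | 5.1 | 5.0 | 5.0 |
| 100 / 600 | – | 4.3 | 5.0 | 5.9 | 5.6 | 5.2 | 5.0 |
| 100 / 680 | 4.8 | – | 4.9 | 6.0 | 5.7 | 5.1 | 5.0 |
| 60 / 720 (extreme) | 4.4 | – | 5.1 | 6.3 | 6.4 | 5.8 | 5.1 |

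A dash marks a cell not run. At 300 vs 600 the peak over all ratios tried is 5.2 to 5.3%. Except in the extreme 60 vs 720 split, the error is back to about 5% by r = 1.3, because the pre-test then rejects in 93% or more of samples.

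**Step 5: small groups, for scale only.** 30 vs 120 gives 6.4 to 6.6% at r = 1.15 to 1.3, and 15 vs 90 gives about 7.9% at r = 1.3.

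**Step 6: the alternative.** Satterthwaite used always gives 4.9 to 5.3% in every cell run.

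**Step 7: its cost in power.** With equal variances and a true difference of 2.8·√(1/n₁ + 1/n₂) SDs (about 80% power), power under the two-stage rule and under Satterthwaite always is:
- 100 vs 600: 79.8% and 79.4%
- 30 vs 120: 79.3% and 78.2%
- 20 vs 100: 79.0% and 77.1%
- 15 vs 90: 78.6% and 75.5%

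**The case against.** The strongest reply is that this is a common textbook rule that already corrects for unequal variances, contradicts nothing in the article, and does no harm at the sizes the article plans. Much of that stands. At 1:1:1 the error is 5% whatever the SD ratio. At cohort scale the pre-test does catch the large variance differences. The comparisons concerned are unadjusted ones between non-randomised cohorts, where confounding is a far larger threat than one point of type I error. What does not stand is that the rule holds 5% in general: it drifts in both directions once sizes and variances both differ.

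A reader might infer more than the article supports:
- **That unequal sizes alone inflate the error.** They do not. With equal SDs every cohort-scale cell is at 4.9 to 5.1%. The larger variance must also lie in the smaller group, and in the reverse case the test is conservative.
- **That cohort sizes will be unequal.** Consecutive enrolment with cohorts defined by treatment makes this plausible, but the article plans 1:1:1 and does not predict a split.
- **That errors of 6.5 to 8% will occur in the PASI strata.** Those figures need t-tests within groups whose smaller arm has about 15 to 30 patients. The strata belong to the adjusted analysis in section 2.10.5, which assigns no t-test to them and gives no stratum sizes.
- **That quality of life, itch or BSA are affected.** They are only if judged normal; otherwise section 2.10.2 sends them to Wilcoxon tests.

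**Conclusion.** The point holds as a minor one. The two-stage rule in section 2.10.2 does not keep the stated 0.05 level when cohort sizes and variances both differ. On assumed inputs, the error is at most about 5.3% at 300 vs 600 and about 5.9% at 100 vs 600 (SD ratio 1.1, larger SD in the smaller group). It falls to about 4.3% at 100 vs 600 when the ratio is 0.9. It is 5% with equal cohorts or equal variances.

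The result rests on normal data, a folded F pre-test, and sizes and SD ratios that the article does not give. The primary outcome in section 2.5.1 is a binary recurrence rate, so neither it nor the adjusted analyses depend on this rule. No principal conclusion of the study is at risk. The case for change is that a better rule is already in the plan and nearly free.

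**What to change.** In section 2.10.2, delete the variance pre-test and state that every two-group comparison of normally distributed quantitative data uses the Satterthwaite (Welch) t-test, whatever the observed variances. If a statistical analysis plan exists, carry the same wording there.

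The change replaces one sentence and needs no new method or data. The power cost with equal variances is under 0.5 points at cohort scale (0.4 at 100 vs 600). It is about 1 to 3 points in very small unequal groups (1.1 at 30 vs 120, 3.1 at 15 vs 90), and nil with equal cohorts.
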